#### Statistical analyses

Analysis of the patients will follow the CONSORT flow diagram (see Fig. 1) through the phases of the study (enrollment (assessed, excluded, randomized), allocation (control group, experimental group with received intervention or not received intervention), follow-up (lost to follow-up, discontinued intervention), and analysis (excluded, included)) [29].

**Fig. 1 Fig1:**
[figure not shown]
CONSORT study flow diagram

The outcomes of the control and experimental group will be analyzed by the repeated measures within-between interactions ANOVA approach and an intention-to-treat analysis (last observation carried forward method). No subgroup analyses are planned.

Primary analysis: For the descriptive analyses means, standard deviations, 95 % confidence intervals, and median, quartiles, minima, maxima will be used.

To compare the primary outcome ICIQ-UIsf between and within the two groups (control group, experimental group) at ten time points (before intervention, physiotherapy sessions 2–9, after intervention), ANOVA models for longitudinal data according to Brunner et al. [30] will be used. All statistical analyses will be realized after the final measurement of the last patient at the time point after intervention. The statistics will be calculated by SPSS and R software packages in the current versions. The repeated measure design with ten time points allows us to monitor how patients change over time, in both short-term (before/during intervention) and long-term situations (before/after intervention).

Secondary and tertiary analyses: All secondary and tertiary outcomes will be analyzed following the same approach and with the same statistical procedures as for primary outcomes. Generally, rational data will be checked for normality using Q-Q-plots. If the normality assumption is not violated, parametric ANOVA models for longitudinal data will be used [31]. As for intra-session retest procedures (EMG amplitude and frequency), data will also be described and checked for their reliability (ICC, SEM, MD, ANOVA).

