### Statistical methods

#### Hypothesis

Alternative hypothesis for primary outcome: It is hypothezised that the experimental group focusing on involuntary pelvic floor muscle contractions will have a statistically higher improvement of continence measured by ICIQ-UIsf questionnaire from before to after the intervention phase.

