#### Sample size calculation

Sample size calculation was performed with G*Power software [27], using the statistical model of an ANOVA approach (repeated measures, within-between interactions). To this day there is no comparable training study (RCT) to estimate sample size based on available data from ICIQ-UIsf. Consequently, sample size was estimated theoretically and an effect size of = 0.1, indicating a small effect [28] will be accepted. The sample size was calculated for the primary outcome ICIQ-UIsf with the following assumptions: α = 0.05, power (1–β error probability) = 0.8, number of groups = 2, number of measurements = 10; correlations among repeated measures were estimated conservatively low with 0.5. Based on these assumptions, a total sample size of N = 80 was estimated. In anticipation of dropouts (10 %: n = 8) or a violation of normality assumption (+10 %: +n = 8), a final sample size of N = 96 (48 participants per group) results.

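### The primary hypothesis is a directional before-to-after difference, but the test planned and powered is a non-directional interaction over ten visits, and no before-to-after contrast is named as decisive

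*Protocol article*

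**What the plan says.** Under Statistical methods, Hypothesis, the protocol article says that the experimental group "will have a statistically higher improvement of continence measured by ICIQ-UIsf questionnaire from before to after the intervention phase". This is one between-group comparison with a direction, running from visit 1 (week −1) to visit 11 (week 16 + 1) in Table 1.

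Under Statistical analyses, outcomes "will be analyzed by the repeated measures within-between interactions ANOVA approach". The paragraph on the primary outcome begins "To compare the primary outcome ICIQ-UIsf between and within the two groups (control group, experimental group) at ten time points" and continues "before intervention, physiotherapy sessions 2–9, after intervention), ANOVA models for longitudinal data", citing a Brunner-type method.

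The Sample size calculation section follows the analysis rather than the hypothesis. It was done "using the statistical model of an ANOVA approach (repeated measures, within-between interactions", with "α = 0.05, power (1–β error probability) = 0.8, number of groups = 2, number of measurements = 10", a correlation of 0.5 and "an effect size of = 0.1, indicating a small effect". It arrives at N = 80, raised to 96.

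The article says that ten time points make it possible to follow short-term and long-term change. That describes the design; it does not define a test.

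**The concern.** The hypothesis uses two of the ten time points and has a sign. A group-by-time interaction over two groups and ten visits has (2 − 1)(10 − 1) = 9 degrees of freedom and no sign. It rejects for any difference in the shape of the two profiles, including one confined to the eight interim sessions and one that favours the control arm.

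Two things are at stake. A significant primary p-value could be reported as support for the hypothesis when the arms do not differ at the end of treatment. And if the omnibus result and the before-to-after difference disagree, the plan does not say which one decides.

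A transient difference is conceivable here. Table 2 shows power training in the experimental arm from week 1, but in the control arm only in weeks 10–16.

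**Working it through.** **Inputs.** From Sample size calculation: effect size 0.1 (its symbol is missing from the text; I read it as Cohen's f), α = 0.05, k = 2 groups, m = 10 measurements, ρ = 0.5, N = 80 and 96. The time points come from Table 1. The article gives no SD, no target difference in points and no time pattern. My assumptions are therefore differences in units of a common SD, equal correlation 0.5, sphericity and two-sided tests at 0.05.

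**Step 1: reproduce the plan's N.** λ = f²·N·m/(1 − ρ), df1 = 9, df2 = (N − 2)·9.

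- N = 78: λ = 0.01 × 78 × 10/0.5 = 15.6, power 0.792.
- N = 80: λ = 16.0, df2 = 702, power 0.805.
- N = 96: λ = 19.2, df2 = 846, power 0.885.

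The smallest balanced N is 80, as stated, and 80 + 8 + 8 = 96. The powered test is thus the 9-df interaction.

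**Step 2: significance without the hypothesised effect.** Let d_t be the between-group difference at time t. With two equal groups, f is half the SD of d_t over the ten time points. Take d_t = 0.40 SD at PT3 to PT7 (weeks 4 to 12) and zero at the other five points, including baseline and visit 11. The SD of d_t is 0.40 × √(0.5 × 0.5) = 0.20, so f = 0.10, exactly the planned effect. The rejection rates are those of Step 1: 80.5% at N = 80 and 88.5% at N = 96. Reversing the sign of d_t leaves λ unchanged. The before-to-after difference is zero, so its test rejects in 5%. A 3,000-run simulation of a Brunner-type rank statistic gave 75% at N = 80.

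**Step 3: power when the end difference D is real.** The SD of a change score is √(2(1 − 0.5)) = 1. With baseline adjustment (ANCOVA) it is √(1 − 0.5²) = 0.866. The noncentrality of the contrast is D/(SD × √(4/N)). For the interaction at N = 80, λ = 1600·f².

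- Linear divergence: the SD of 0, 1/9, …, 1 is 0.319, so f = 0.1 implies D = 0.2/0.319 = 0.627.
- Immediate and sustained, or last visit only: the SD is 0.30·D, so D = 0.5 gives f = 0.075 and λ = 9.0.
- Linear with D = 0.5: f = 0.080, λ = 10.2.
- Last five time points only: the SD is 0.5·D, so D = 0.40 gives f = 0.10.

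| Pattern, N = 80 | Interaction | Change score | ANCOVA |
|---|---|---|---|
| Linear to 0.63 SD | 80% | 79% | 89% |
| Linear to 0.5 SD | 57% | 60% | 72% |
| Immediate sustained, or last visit only, 0.5 SD | 50% | 60% | 72% |
| Last five time points, 0.40 SD | 80% | 42% | 53% |

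In the 0.5 SD rows the rank statistic gave 43–51% in simulation.

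**Step 4: patients needed for a direct contrast at D = 0.5 SD, 80% power.** The change score needs 63 per arm (126 in total). ANCOVA needs 48 per arm (96 in total): noncentrality 0.5/(0.866 × √(4/96)) = 2.83, power about 80%. If 8 of the 96 are lost, the noncentrality is 0.5/(0.866 × √(4/88)) = 2.71, power about 76%.

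**The case against.** The analysis and sample-size sections agree with each other, and N = 80 is correct for the test it was computed for. The stated aim is also broader than the hypothesis: to compare the effect of two programmes on incontinence, with interest in the course during treatment as well as the end. A profile test speaks to that aim. Contrasts and the form of the effect estimate can be left to an analysis plan, and modelling baseline as a repeated outcome is a legitimate choice. All of this stands. It does not remove the mismatch, because the hypothesis and the test are both stated in the article and differ.

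Three stronger readings are tempting and are not supported:

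- **That the interaction test always loses power.** Against the unadjusted change score it loses nothing under linear divergence at f = 0.1 (80% against 79%), and it wins for the late-onset pattern. In the linear case the gain to 89% comes from baseline adjustment, a separate choice.
- **That false success is near certain.** A higher rate needs a transient effect larger than the planned f = 0.1.
- **That the primary p-value says nothing about the trial's question.** It answers a broader and less specific one.

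The figures use the parametric F test, whereas the article cites a Brunner-type method for the primary outcome. The simulated rank statistic lowers the Step 2 figure from about 80% to 75%, which does not change the conclusion.

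**Conclusion.** The point holds as a mismatch between hypothesis and primary test. At the planned effect size, a purely transient difference produces a significant primary result in about 80% of trials at N = 80 and 88% at N = 96, in either direction, with no difference at the end of treatment. The cost in power is secondary and depends on the pattern: for an end difference of 0.5 SD that develops linearly, at once or only at the last visit, the interaction has 50–57%, the change score 60% and the baseline-adjusted contrast 72% at N = 80.

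These sizes rest on equal correlation 0.5, sphericity, the parametric F test and time patterns that I chose. That the interaction is the effect to be tested is read from the model named and from the sample-size calculation, since the primary-analysis sentence does not single out an effect. The size of the recruitment target is not shown to be wrong.

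**What to change.** Name one primary test: the between-group difference in ICIQ-UIsf at visit 11 (week 16 + 1), adjusted for baseline ICIQ-UIsf and reported in points with a 95% CI. It can be estimated by ANCOVA or as the visit-11 contrast of a longitudinal model. Keep the ten-point group-by-time profile and the within-group changes as supportive.

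Restate the Sample size calculation for that contrast. No patients need to be added: N = 96 gives about 80% power for 0.5 SD with ANCOVA at correlation 0.5, before dropout. State the target difference directly rather than carrying f = 0.1 over. With two time points f = D/4, so 0.1 would mean D = 0.4 SD and a total of 200.

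The data are already scheduled. The cost is a dated amendment to the primary analysis before unblinding, since randomization began on 11 March 2015, together with the rewritten sample-size paragraph. The downside is that the profile test becomes supportive, and the late-onset patterns that it detects better are no longer tested as primary.

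### The pre-intervention ICIQ-UIsf is modelled as one of ten response levels rather than conditioned on, so a valid primary test gives up precision and lets chance baseline imbalance into the treatment contrast

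*Protocol article*

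**What the plan says.** Under Statistical analyses, the Protocol article states that outcomes "will be analyzed by the repeated measures within-between interactions ANOVA approach". It compares the primary outcome "at ten time points (before intervention, physiotherapy sessions 2–9, after intervention), ANOVA models for longitudinal data". The abstract lists the same ten time points, and Table 1 marks ten ICIQ-UIsf measurements for the primary outcome, with the baseline visit as the first.

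The sample size section is built on the same structure: "number of groups = 2, number of measurements = 10", "α = 0.05, power (1–β error probability) = 0.8", and "correlations among repeated measures were estimated conservatively low with 0.5".

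The Hypothesis section words the target as a "statistically higher improvement of continence measured by ICIQ-UIsf questionnaire from before to after the intervention phase".

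The model carries over to the other endpoints: "All secondary and tertiary outcomes will be analyzed following the same approach and with the same statistical procedures as for primary outcomes".

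Nowhere does the article name the baseline score as a covariate, constrain the arm means to be equal at baseline, or describe stratifying the 1:1 allocation by baseline severity. The role of baseline is therefore fixed in the article and not left open for a later analysis plan.

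**The concern.** Women are randomised, so the true mean ICIQ-UIsf before treatment is the same in both arms, and any observed difference there is noise. A group-by-time interaction that includes baseline as a level does not use this knowledge. It estimates a separate baseline mean for each arm and measures divergence across all ten levels, including that noisy one.

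Two things are at stake. The first is precision, which the trial could have at no cost because the baseline score is already collected. The second is the answer in the one trial that is run. If one arm starts worse by chance, regression to the mean makes it appear to improve more. Averaged over many randomisations this cancels, but in a single trial of 48 per arm it does not.

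**Working it through.** **Inputs.** From the sample size section: effect size 0.1 (read as Cohen's f), α 0.05, power 0.8, two groups, m = 10 measurements, correlation ρ = 0.5, N = 80, raised to 96 (48 per arm). From Table 1: ICIQ-UIsf weeks −1, 2, 4, 6, 8, 10, 12, 14, 16 and 17. Assumed here: compound symmetry, normal errors, a second correlation of 0.8, and the effect trajectories below.

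**1. The plan's own figure.** For a within-between interaction the noncentrality is λ = f²·N·m/(1−ρ) = 0.01 × 80 × 10/0.5 = 16, with 9 and (80−2) × 9 = 702 degrees of freedom. Power is 0.805; N = 78 gives 0.792. N = 80 reproduces, with baseline counted among the ten levels.

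**2. The before-to-after contrast.** Per-woman variance in units of σ²:
- change from baseline: 2(1−ρ);
- baseline as covariate: 1−ρ²;
- ratio: (1−ρ²)/[2(1−ρ)] = (1+ρ)/2.

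At ρ = 0.5 this is 0.75/1.00 = 0.75. The standard error ratio is √0.75 = 0.866, a 13% reduction. At ρ = 0.8 it is 0.36/0.40 = 0.90, a 5% reduction. At ρ = 0.9 it is 0.95.

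**3. Chance imbalance.** With 48 per arm the baseline difference has standard deviation √(2/48) = 0.20 outcome SDs, and it exceeds 0.2 SD in either direction in about 33% of trials. An imbalance of 0.2 SD shifts the change contrast by (1−ρ) × 0.2: 0.10 SD at ρ = 0.5 and 0.04 SD at ρ = 0.8. Conditioning on baseline removes this shift.

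**4. The planned ten-level interaction.** Let d be the vector of true arm differences, zero at baseline. Apart from a common factor:
- planned interaction: λ ∝ Σd² − (Σd)²/10;
- nine post-baseline differences given baseline: λ ∝ Σd² − [ρ/(1+9ρ)]·(Σd)².

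The multiplier of (Σd)² in the second line is 0.0909 at ρ = 0.5 and 0.0976 at ρ = 0.8, against 0.1 in the first. Example, an immediate step (d = 1 at all nine visits, so Σd² = 9 and (Σd)² = 81) at ρ = 0.5: 9 − 8.1 = 0.90 against 9 − 7.364 = 1.636. The ratio is 1.818, so λ rises from 16 to 29.1.

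In every row the planned test is scaled to λ = 16 (power 0.805), and the reference F has 9 and 702 degrees of freedom:

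| Trajectory of the arm difference | λ, ρ = 0.5 | Power, ρ = 0.5 | λ, ρ = 0.8 | Power, ρ = 0.8 |
|---|---|---|---|---|
| Final visit only | 16.2 | 0.81 | 16.0 | 0.81 |
| Last three visits | 16.6 | 0.82 | 16.2 | 0.81 |
| Quadratic growth over visits | 17.6 | 0.85 | 16.4 | 0.82 |
| Ramp, equal steps per visit | 19.6 | 0.89 | 17.0 | 0.83 |
| Ramp by calendar week from week −1 | 20.2 | 0.90 | 17.1 | 0.84 |
| Immediate step | 29.1 | 0.98 | 19.5 | 0.89 |

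**5. Validity.** In a simulation of 3,000 null trials with 40 per arm and ρ = 0.5, the planned interaction rejected in 4.7%, in line with the nominal 5%.

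**6. Three-visit secondary outcomes** (baseline, after intervention, follow-up), sustained effect: Σd² = 2 and (Σd)² = 4. The planned term is 2 − 4/3 = 0.667. Given baseline at ρ = 0.5 it is 2 − (0.5/2) × 4 = 1.0. The noncentrality rises by 50%; at ρ = 0.8 it rises by 15%.

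**The case against.** The strongest reply is that the plan contains no error. The test holds its level, the contrast is unbiased over randomisations, and the trial is sized on the model it will fit. All of that stands: this is a matter of efficiency and of conditional bias, not of validity or arithmetic.

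A reader might infer from the variance ratio of 0.75 that 96 women would work like 128 (96/0.75). A reader might also infer that power would rise from 68% to 80% for an assumed true difference of 0.5 SD. Both figures describe a single before/after contrast. The analysis that the article fixes is the ten-level interaction, in which baseline is one level of ten, so its noise does not enter in full. There the gain is almost nil if the arms separate only at the end. The 98% figure needs the whole between-arm effect to be present at the second physiotherapy session in week 2, which is an extreme case for a staged 16-week programme.

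The correlation also matters. The article calls 0.5 conservatively low, so a higher value is to be expected and the benefit shrinks with it. Finally, the calculations are parametric. The longitudinal ANOVA that the article cites shares the group-by-time structure, but its own loss was not computed.

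One part of the reply does not stand: that an unseen analysis plan may deal with this. Such a plan might add an adjusted sensitivity analysis, but the article already makes baseline a response level in the primary analysis and in the sample size.

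**Conclusion.** The point holds as an efficiency weakness that is worth correcting. Treating baseline as a response level costs precision and leaves the result open to chance imbalance. For the hypothesised before-to-after contrast, the variance with baseline as covariate is 0.75 of the variance of the change score at the plan's correlation and 0.90 at 0.8.

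For the planned interaction, the gain over about 80% power runs from negligible (late effects) through moderate (ramps, up to about 0.90 at correlation 0.5 and 0.84 at 0.8) to large only for an immediate step. The direction of the gain does not depend on the trajectory, but its size does.

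The figures assume compound symmetry, normal errors, complete data and, for the interaction, N = 80. They do not show that the primary test is biased or has the wrong error rate, and they give no exact loss under the cited longitudinal method.

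**What to change.** Take the pre-intervention score out of the response. Fit the nine post-baseline ICIQ-UIsf visits with arm, visit, arm-by-visit, baseline and baseline-by-visit. Alternatively, keep ten visits and constrain the baseline means to be equal across arms. Once baseline has left the response, the overall test must cover arm and arm-by-visit jointly (9 degrees of freedom), because arm-by-visit alone would miss a constant effect. Report the baseline-adjusted arm difference after the intervention in ICIQ-UIsf points with its 95% CI.

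If a rank-based method is kept, adjust for baseline by rank analysis of covariance. Treat every secondary and tertiary outcome with a baseline value in the same way: EMG, pad test, ICIQ-LUTSqol and manual muscle testing. Adherence has no baseline value and is unaffected.

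The cost is one paragraph in the analysis plan, written before unblinding. No further patients, visits or measurements are needed, and the planned analysis can be kept as a sensitivity analysis.

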### Blinding

Participants will be blinded against the type of received physiotherapy (control group, experimental group). The participant information document will not provide any information regarding the differences in the experimental and control therapy protocols in a way that women could find out about their group allocation. All investigators involved in data acquisition, data reduction, data analyses, and statistics will also be blinded against group allocation. The physiotherapists in charge of the therapy cannot be blinded against group allocation and therefore will not be involved in data acquisition, data reduction, data analyses, or statistics.

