#### Outcome measurements

Baseline (before intervention phase), after intervention phase, and 6-month follow-up measurements (of primary, secondary, and tertiary outcomes) will take place at the Bern University of Applied Sciences movement laboratory by two experienced pelvic floor physical therapists, who are blinded regarding group allocation of participants. Measurements during the 16-week intervention phase (ICIQ-UIsf; primary outcome) will be taken by the treating physiotherapists. However, to guarantee blinding of the outcome, the participant will fill in the questionnaire in the absence of the treating physiotherapist and seal it in an envelope, which will be given to the outcome assessor.

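### The only stated analysis time falls 25 weeks before the last 6-month visit, so the 6-month outcomes that the protocol plans to analyse would be incomplete

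*Protocol article*

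**What the plan says.** In the Statistical analyses section, the paragraph on the primary analysis compares the ICIQ-UIsf "at ten time points (before intervention, physiotherapy sessions 2–9, after intervention), ANOVA models for longitudinal data according to Brunner et al. [30] will be used". The next sentence sets the timing: "All statistical analyses will be realized after the final measurement of the last patient at the time point after intervention". The following paragraph adds: "All secondary and tertiary outcomes will be analyzed following the same approach and with the same statistical procedures as for primary outcomes". The section also specifies an intention-to-treat analysis with last observation carried forward.

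Table 1 puts the post-intervention visit (visit 11) at week 16 + 1 and the 6-month follow-up (visit 12) at week 16 + 26. Visit 12 repeats the EMG measurements, ICIQ-LUTSqol, pad test, manual muscle testing and adherence. It also includes the ICIQ-UIsf, which Table 1 lists as a secondary outcome at that visit. The Outcome measurements section confirms the schedule: "Baseline (before intervention phase), after intervention phase, and 6-month follow-up measurements (of primary, secondary, and tertiary outcomes) will take place", by two therapists "who are blinded regarding group allocation of participants". The Blinding section states: "All investigators involved in data acquisition, data reduction, data analyses, and statistics will also be blinded against group allocation".

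The abstract and the Study design section both present the 6-month follow-up as part of the design.

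**The concern.** The timing sentence covers every statistical analysis and ties them all to visit 11. The schedule collects secondary and tertiary outcomes at visit 12, and the plan says that all such outcomes will be analysed. Both statements cannot be carried out as written.

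The 6-month comparison is at stake. If it is run at the stated time, women who have not yet reached visit 12 have no 6-month value. Carrying their last value forward treats them as if nothing changed after the intervention, although they are still in follow-up. Leaving them out restricts the 6-month result to women recruited earlier.

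There is a second, weaker risk. Digital strength grading rests on judgement and the questionnaires on self-report, and home training continues until visit 12. If group results circulated during that period, they could influence these measures.

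**Working it through.** **Inputs from the protocol article**
- Visit 11: week 16 + 1 = 17 (Table 1).
- Visit 12: week 16 + 26 = 42 (Table 1).
- Sample size: 80 + 8 + 8 = 96 (Sample size calculation). The 80 reproduces from the stated inputs, reading the effect size as Cohen's f and assuming sphericity: noncentrality 0.1² × 80 × 10 / (1 − 0.5) = 16, with 9 and 78 × 9 = 702 degrees of freedom, gives power 0.805; N = 78 gives 0.792. The timing point uses only the 96.
- First randomisation: 11 March 2015 (Trial status). Neither the recruitment rate nor its duration is stated.

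**Gap.** 42 − 17 = 25 weeks.

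**Who is still pending.** Let the last woman be randomised at week T of recruitment, and assume the same interval from randomisation to start of training for all women. The stated analysis time is T + 17. A woman randomised at week t reaches visit 12 at t + 42. She is pending if t + 42 > T + 17, that is, if t > T − 25. The last woman always meets this condition, so the number pending is never zero.

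**How many.** With even accrual over T weeks (T of at least 25) and no dropout, the number pending is about 96 × 25 / T. T is an assumption throughout.

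| Assumed T (weeks) | 96 × 25 / T | Share of 96 |
|---|---|---|
| 26 | 92.3 | 96% |
| 52 | 46.2 | 48% |
| 78 | 30.8 | 32% |
| 104 | 23.1 | 24% |
| 156 | 15.4 | 16% |

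**Carry-forward.** In Table 1 the last measurement before visit 12 is visit 11 for each outcome repeated at visit 12. For a pending woman, last observation carried forward therefore enters the week-17 value as the week-42 value. Under the middle three assumptions this affects 24% to 48% of the sample before any true dropout is counted.

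**Primary outcome.** Its ten time points end at visit 11. Its data are complete at the stated time, so nothing here affects the primary analysis.

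**The case against.** The best defence is where the sentence stands. It is in the primary-analysis paragraph, directly after the ten primary time points, and the secondary and tertiary analyses have their own paragraph. On that reading the primary analysis simply waits until every woman has reached its last time point, which is sound practice. A condensed article may also leave the date of the 6-month analysis and the release of results to a fuller document.

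This is a plausible account of what was intended, but it does not settle the matter. The sentence says all analyses, and the sentence after it, on software, reads as trial-wide. The same paragraph describes the long-term comparison as before versus after the intervention, without month 6. The finding is therefore that a stated rule conflicts with the stated schedule, not that a detail is missing.

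Three stronger readings are tempting, and the documents do not support them.
- A reader might infer that group results will be known during follow-up and that the triple blinding then fails. No disclosure is described. Assessors and those handling data and statistics are blinded to allocation, and the allocation envelopes are kept at an independent secretariat. An aggregate result does not reveal any woman's group. The Blinding section speaks of allocation and not of knowledge of results, so the risk is possible but not established.
- A reader might infer that no 6-month data could enter the analysis. Women randomised more than 25 weeks before the last one could already have theirs; the data would be incomplete, not absent.
- A reader might take the pending counts as facts or as a measure of bias. They count visits still due and depend on an assumed accrual period.

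**Conclusion.** The point holds as an internal contradiction. The one analysis time that the protocol gives falls 25 weeks before the last 6-month visit, while the protocol also plans to analyse the outcomes of that visit. The 25 weeks follow from Table 1 alone. About 46, 31 or 23 of 96 women would be pending for accrual over 52, 78 or 104 weeks, assuming even accrual and no dropout. The number is uncertain but cannot be zero.

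The firm consequence is for the 6-month analysis: if the timing sentence and the carry-forward rule are followed literally, week-17 values stand in for 6-month values in women who are not dropouts. Influence of known group results on the follow-up measures is a possibility to guard against, not a demonstrated flaw. The primary analysis and the sample size are unaffected. The wording should be corrected before any analysis is run.

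**What to change.** Replace the timing sentence with three statements.
1. The primary analysis is run after the last visit 11, on locked data and with coded arms. This is in line with the existing Blinding section.
2. The 6-month outcomes are analysed after the last visit 12. Carry-forward, if kept, then applies only to women who truly lack that visit.
3. Group results are withheld from the outcome assessors, the treating physiotherapists and the participants until the last visit 12 is complete.

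This changes no visit, no outcome and no sample size. The cost is protocol wording and a delay of up to about 25 weeks before results can be shared.
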